## Abstract

**Background:**

Third and fourth degree perineal tears, or obstetric anal sphincter injuries (OASI), sustained during childbirth can result in anal incontinence and psychosocial problems which require ongoing treatment. Within the English National Health System (NHS) reported rates of OASI have gradually increased. In response, a care bundle was developed incorporating four elements: 1) antenatal information to women, 2) manual perineal protection during all vaginal births, 3) episiotomy to be performed with a 60° mediolateral angle at crowning (when clinically indicated) and 4) perineal examination (including per rectum) after childbirth. Implementation of the OASI Care Bundle is aided by a skills development module and an awareness campaign. The project is a collaboration between two national professional bodies, an NHS hospital trust and an academic institution.

**Methods:**

Implementation of the OASI Care Bundle will be evaluated using a stepped-wedge design. From January 2017 sixteen maternity units across England, Wales and Scotland will participate in the study over a 15-month period, with sequential roll-out of the intervention in four blocks (regions) of four units. The primary clinical outcome is OASI rate. Regression analysis will adjust for differences in organisational characteristics and obstetric risk factors in women who gave birth before and after implementation of the care bundle. Focus group discussions and in-depth interviews with clinicians will evaluate the feasibility of integrating the care bundle into routine practice. Interviews with women will explore the acceptability of the intervention.

**Discussion:**

This protocol outlines the evaluation of our quality improvement project which aims to prevent OASI using a bundle of evidence-based interventions that are each widely used in practice. The OASI project aims to 1) standardise practice to prevent OASI in a way that is acceptable to clinicians and women and 2) identify the barriers and enablers associated with upscaling interventions within maternity units. If found to be effective, feasible and acceptable, the OASI Care Bundle will be shared with a range of audiences using the communication channels available to the professional bodies.

**Trial registration:**

The OASI Project was retrospectively registered on the ISCTRN12143325 database date assigned 03/10/2017.

## Background

The rates of recorded obstetric anal sphincter injuries (OASI) among primiparous women have tripled in the English National Health Service (NHS) from 1.8% in 2000 to 5.9% by 2011, with 70,000 women being affected during this period [1]. An OASI is defined as any degree of injury to the anal sphincter muscle sustained during childbirth. Short-term consequences of OASI include pain, bleeding and infection, which can result in urinary retention and constipation [2]. Long-term consequences include urinary and faecal incontinence, chronic pain and painful intercourse. Such morbidities can have a severe psychosocial impact and affect future birth choices [3]. Furthermore, there are significant cost implications for the NHS associated with further treatment and negligence claims relating to OASI between 2000 and 2010 are estimated to total £31.2 million [4]. OASI rates are also increasing in several countries including Australia, China and Canada [5–7]. Such trends render OASI prevention a quality improvement priority for maternity units across the world.

The aetiology of OASI is multifaceted and known risk factors include; birthweight greater than 4 kg, persistent occipito-posterior position, primiparity, induction of labour, prolonged second stage and an instrumental (assisted) birth [8, 9]. Research has shown that training gaps amongst midwives and obstetricians and a lack of awareness of risk factors may contribute to the increase in OASI rates [10–16]. Variations in practice, with increasing use of a “hands-poised” approach to protecting the perineum during childbirth as opposed to a “hands-on” approach are also thought to be contributing factors [1]. Not all perineal injuries are preventable, however, evidence from Scandinavia and small-scale studies in England show that OASI rates can be significantly reduced [10, 11, 17–19]. For instance, in Norway, the OASI rate decreased from 4.0 to 1.9% after the introduction of a package of interventions [10].

In light of the rising trends in OASI rates in England, a team of national experts met to discuss strategies to reverse this trend. There was unanimous agreement that there was potential for a ‘care bundle’ of evidence-based actions to be developed. A joint statement supporting this work was produced by the Royal College of Obstetricians and Gynaecologists (RCOG) and the Royal College of Midwives (RCM) [20].

With this in mind, two main objectives were established:To develop and implement a care bundle to reduce third and fourth degree perineal tearsEvaluate outcomes associated with implementing a care bundle

We report the development of the OASI Care Bundle; and the design of the prospective evaluation of the care bundle across maternity units in England, Wales and Scotland.

### Development of the OASI care bundle

Care bundles are described by the US Institute for Healthcare Improvement as a collection of interventions that need to be delivered together in order to provide effective and safe care for patients [21]. Within the NHS, care bundles are increasingly being developed to improve outcomes [22]. For a care bundle to be most effective, it should be concise, straightforward and comprise of three to five evidence-based practices [21]. The novelty of the approach is that is combines elements of good practice into one cohesive package that, when implemented, improves the reliability and quality of care, and in turn, patient outcomes.

Figure 1 shows the stepwise development of the care bundle which began with a summit of national experts and the formation of a working group (the OASI Care Bundle group) in May 2014. Following this, a literature review of intrapartum interventions that might impact OASI rates was conducted. Over 2000 studies were identified using a comprehensive search strategy within EMBASE, Ovid Medicine, Cochrane, CINAHL and the Maternity and Infant Care database. Studies that were included for review were randomised, or quasi-randomised, trials of interventions that are used in the second stage of labour with OASI as an outcome. Results were supplemented by narrative reviews of key non-randomised studies.

**Fig. 1 Fig1:**
[figure not shown]
Development of the OASI Care Bundle. This shows the stepwise development of the care bundle which began with the summit of national experts and the formation of a working group (the OASI Care Bundle group) in May 2014

The results of the review and recommendations from pre-existing UK guidelines [9, 23] were presented to the OASI Care Bundle group, comprising of clinical and methodological experts with representatives from the RCOG, RCM and the London School of Hygiene and Tropical Medicine (LSHTM). This led to a structured discussion about the clinical practicalities of each individual care bundle element. The four elements finally included by the OASI Care Bundle group were:Women to be given information during the antenatal period about perineal trauma and how to minimise their risk of sustaining an OASI.When clinically indicated, a mediolateral episiotomy should be performed at a 60-degree angle to the midline at crowning.Documented use of Manual Perineal Protection (MPP) for:All spontaneous vaginal births, unless the woman’s chosen birth position does not allow for it (e.g. water birth)All instrumental vaginal births (e.g. forceps, ventouse and kiwi)Following birth, the perineum should be examined and any tears graded in accordance to RCOG guidelines [9]. The examination should include a per rectum check, even if the perineum appears intact.

Following presentations to the RCM and other leaders of labour care and birth, changes were made to the care bundle manual and the training materials to emphasise support for women’s birth choices, the importance of mobility during labour and natural birth physiology.

In January 2015, a survey was sent to all UK maternity units to assess their interest in piloting the OASI Care Bundle. From the 91 units who responded, two were chosen to carry out a three month pilot study. The main aim of the pilot was to determine whether the care bundle was acceptable and feasible for clinicians. Following the pilot study, funding was obtained from the Health Foundation to adapt and scale-up the OASI Care Bundle as a quality improvement project, to be implemented in sixteen maternity units across England, Wales and Scotland; this forms the current project.

### Implementation of the OASI care bundle

Implementation of the OASI Care Bundle is supported with a skills development module and a communications and awareness campaign. Additionally, sustained leadership and support is provided by professional organisations and the Project Team. This quality improvement project aims to optimise implementation by addressing knowledge gaps regarding the prevention of OASI; in particular inconsistencies in training, skills and practice. Local implementation of the project is led by clinical champions (midwives and obstetricians) within each unit. The champions receive multi-disciplinary training at designated RCOG Skills Development Days (organised and delivered by our Project Team) on the key elements of the care bundle, and they then cascade the training and educational materials to their colleagues in their units. This train-the-trainer approach aims to ensure that all clinicians are trained within the unit within the three month transition phase, thereby achieving adequate enrolment of women to the intervention. Further skills development is provided by the project clinical leads who visit each unit approximately four to six weeks after the start of implementation. A detailed Theory of Change has been developed in conjunction with OASI Care Bundle group (Fig. 2). A number of inter-related implementation optimisation strategies [24] for the bundle have also been articulated (Fig. 3).

**Fig. 2 Fig2:**
[figure not shown]
The Theory of Change. This shows our detailed Theory of Change which was developed in conjunction with OASI Care Bundle group

**Fig. 3 Fig3:**
[figure not shown]
OASI Care Bundle Implementation Optimisation Strategies. This shows the inter-related implementation optimisation strategies for the care bundle

### Study design and participants

The overall aim of this quality improvement project is to reduce OASI rates. Secondary outcome measures are acceptability (satisfaction with the intervention), feasibility (extent to which intervention can be applied), coverage (extent to which the population receive the intervention) and sustainability (extent to which intervention is maintained).

#### Study setting

To ensure representation across regions, England, Wales and Scotland were divided into four geographical blocks as follows:Region 1: London, South East Coast, Wessex, Thames ValleyRegion 2: Cheshire and Mersey, South West, West Midlands, WalesRegion 3: East Midlands, East of England, Yorkshire and the HumberRegion 4: Greater Manchester, North, Scotland

The 91 units which had expressed an interest in taking part in the pilot study were used for the selection process for the scale-up. Within each region, four units were selected to obtain a total of sixteen units, aiming for at least one from each of the clinical senates in the region, at least one from each of the four maternity unit size categories (defined by the National and Perinatal Audit as < 2500, 2500–3999, 4000–5999 and 6000+ births per year [25]) and at least one from each of the three types of maternity units; namely obstetric-led (hospital based care where obstetricians take responsibility for high-risk women and midwives take responsibility for low-risk women), alongside midwifery units (where midwives provide care for low-risk women in co-located units in the same building as an obstetric unit) and freestanding midwifery unit (often called ‘birth centres’, these are geographically separate from obstetric units and midwives provide care for low-risk women) [26]. A list of the sixteen study units can be found on the ISRCTN database.

All vaginal births are potentially eligible for the intervention when the attending clinician (midwife or obstetrician) has been trained to use the care bundle. Women are excluded if they are in a birthing position that makes it impossible to implement all aspects of the care bundle (e.g. water birth). Given an average number of 304 deliveries per month in each unit, a target of 70% of clinicians having been trained (i.e. deliveries being eligible) and the assumption of up to 10% vaginal deliveries being excluded due to birthing positions, the estimated number of women potentially eligible to receive the care bundle intervention is 32,800 (Table 1).

**Table 1 Tab1:** Design of the stepped wedge trial for OASI Care Bundle evaluation

Region	Time					
	0	1	2	3	4	5
1		Roll-out	3280	3280	3280	3280
2			Roll-out	3280	3280	3280
3				Roll-out	3280	3280
4					Roll-out	3280

## Methods

The study has a stepped-wedge design with complete, continuous recruitment [27]. In stepped-wedge designs, the short-exposure intervention is implemented at the healthcare provider level and staggered in blocks.

The four regions were sequentially randomised to the intervention, using a random number generator. The first region was initiated in January 2017, and the intervention was introduced to remaining regions every three months. The units were informed of their allocation two months before the start of their roll-out period in order to allow for preparation time. The first three months of the intervention is the ‘transition phase’, which is when the care bundle launched at the units, and the local champions cascade the skills development module to their colleagues.

Mixed methods will be used to assess the clinical effectiveness and the implementation outcomes of the OASI Care Bundle. Clinical outcomes will be assessed via routinely collected patient-level data, captured through each unit’s Maternity Information System (MIS). Implementation outcomes will be assessed through specific qualitative and quantitative methods, which will provide a detailed evaluation of the acceptability, feasibility, coverage and sustainability of the intervention.

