#### Data analysis

In stepped-wedge designs, power calculations need to take into account both the clustered nature of the design and the confounding effect of time [30]. The statistical power for the study was calculated using the “steppedwedge” command in STATA 14 [31]. The “steppedwedge” command, written by Hemming and Girling [32] and based on the approach proposed by Hussey and Hughes [33], allows for power and detectable-difference calculations for binary outcomes, following the specification of the number of clusters (units) at each step, the number of steps, the average cluster (unit) size, and the intra-cluster correlation coefficient (ICC, rho). In this study, the number of steps and the number of units per step are both four, totalling 16 units. Unit sizes (the number of vaginal deliveries in each participating unit) were available from national maternity statistics data for each country [28, 34, 35]. There were on average 304 vaginal births a month for each participating unit (with a range of 113–539) in 2014/2015, therefore the average cluster size was 912 vaginal deliveries per unit in a three-month period (duration of each step). The baseline OASI rate and the intra-cluster correlation (ICC, rho) were calculated from English maternity clinical indicators data for 2013/14 [36]. For the 13 participating English units, the OASI rate for all vaginal deliveries was 3.2% and the ICC was 0.0062 (CI:0.0018 to 0.0214). The statistical power of the study to detect a 25% reduction in OASI rate (from 3.2 to 2.4%) is 0.92. Under various scenarios (e.g. using lower confidence interval value for ICC, a cluster size of 700 or a baseline OASI rate of 2.8%), the statistical power remains over 80%.

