In stepped-wedge studies, the proportion of units exposed to the intervention gradually increases, meaning that unexposed observations will, on average, be from an earlier calendar time than exposed observations [30]. Furthermore, improved reporting and increased awareness of the care bundle over the period is likely to have an impact on the OASI rates [1]. Thus, calendar time is associated with both the exposure to the intervention and also the outcome, and is therefore a potential confounder. We will use logistic mixed effects regression to model the log odds of sustaining an OASI, with a fixed effect for each step and a random effect to account for clustering at the unit level [33, 37]. The model will include a linear secular trend and also adjust for risk factors for OASI (maternal age, BMI, ethnicity, mode of delivery, episiotomy, birthweight, prolonged labour, and shoulder dystocia) [1].

Additional analyses are planned subject to completeness and quality of data collected for monitoring purposes throughout the study, including data on care bundle compliance, either on a paper form or electronically. In addition, these summary measures of organisational readiness and trends in the uptake of the intervention (i.e. percentage of clinicians trained and compliance rate) may also be used to explore the impact of these organisational factors on clinical outcomes.

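### Allocation is by four regions, but power and the primary model use 16 units with only a unit intercept, so the nominal error rate and the power of 0.92 hold only if unit and regional rates have no time variation of their own

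*Protocol article*

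**What the plan says.** On allocation, Methods states: "The four regions were sequentially randomised to the intervention, using a random number generator". One region starts every three months. Study setting adds: "Within each region, four units were selected to obtain a total of sixteen units". Units were thus chosen within regions and not randomised one by one.

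On power, Data analysis uses the Stata stepped-wedge command, "based on the approach proposed by Hussey and Hughes [33], allows for power and detectable-difference calculations for binary outcomes". The clusters are the units: "the number of steps and the number of units per step are both four, totalling 16 units". The inputs are 912 vaginal births per unit per quarter, a baseline OASI rate of 3.2% and a between-unit ICC of 0.0062 (interval 0.0018 to 0.0214). The result is: "The statistical power of the study to detect a 25% reduction in OASI rate (from 3.2 to 2.4%) is 0.92". The scenarios cited as keeping power above 80% are the lower ICC limit, a cluster size of 700 and a baseline rate of 2.8%.

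On the model, Data analysis specifies a logistic mixed model "with a fixed effect for each step and a random effect to account for clustering at the unit level", with a linear secular trend and individual risk factors. It names no region, region-by-period or unit-by-period term.

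**The concern.** A unit random intercept with time effects common to all units says that each unit's underlying rate sits at a fixed distance from a shared time course. Only exposure and measured case mix may move it. If units drift separately, or the four units of a region drift together, that movement is left to binomial sampling error. A logistic model has no free residual variance to take it up, so the standard error of the intervention effect comes out too small.

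Allocation by region sharpens this. With one region per step, drift shared by a region's four units coincides with the exposure contrast and is not averaged over independent units. Data analysis itself expects changes in reporting and awareness to affect OASI rates over time, and nothing ensures that these changes are the same in every unit.

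At stake are the coverage of the primary confidence interval, the false-positive rate and the stated power. The article's power scenarios do not test this assumption. They vary the ICC, to which power in this design is almost insensitive, and leave the between-period correlation untouched.

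**Working it through.** **Inputs from Data analysis.** 16 units, 4 per step, 4 steps; m = 912; rates 3.2% and 2.4% (difference 0.008); ICC ρ = 0.0062 (0.0018 to 0.0214). **Assumed:** two-sided 5%, because the article states no alpha; 5 periods with no roll-out gap; a linear approximation for unit-period rates.

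**1. Reproduce 0.92.** Total variance σ² = 0.032 × 0.968 = 0.030976. Between-unit variance ρσ² = 0.0062 × 0.030976 = 0.000192 (SD 1.39 percentage points). Sampling variance of a unit-period rate is (1 − ρ)σ²/m = 0.0000338 (SD 0.58 points). With 16 independent units, a unit intercept and categorical periods, the generalised least squares SE of the effect is 0.002345. Power = Φ(0.008/0.002345 − 1.96) = Φ(1.45) = 0.927. This agrees with 0.92 and confirms that the figure treats the units as independent, with no drift.

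**2. Power against the ICC.** The same calculation gives 0.936 at ρ = 0.0018 and 0.927 at both 0.0062 and 0.0214. The lower limit slightly raises power, so it is not a stress test. A cluster size of 700 gives 0.85. A baseline of 2.8% with the same 25% reduction gives 0.89.

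**3. Unit-by-period variation.** Keep the total between-unit variance and let a share s vary by unit and period, so that the cluster autocorrelation is 1 − s. Take the true SE of the planned estimator (sandwich form) over its model SE as the ratio. Type I error = 2[1 − Φ(1.96/ratio)]. Power is for the estimator with the correct variance.

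| s (autocorrelation) | SE ratio | Type I error | Power |
|---|---|---|---|
| 0 (1.00) | 1.00 | 5.0% | 0.93 |
| 5% (0.95) | 1.13 | 8.3% | 0.86 |
| 10% (0.90) | 1.25 | 11.6% | 0.78 |
| 20% (0.80) | 1.45 | 17.7% | 0.66 |

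These rows are at ρ = 0.0062. For the 10% share, type I error is 6.7% at ρ = 0.0018 (ratio 1.07) and 25.6% at ρ = 0.0214 (ratio 1.73).

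**4. Region-by-period variation**, shared by the four units of a region, at ρ = 0.0062:

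| Share | SD (points) | SE ratio | Type I error | Power |
|---|---|---|---|---|
| 1% | 0.14 | 1.11 | 7.6% | 0.87 |
| 5% | 0.31 | 1.45 | 17.8% | 0.66 |
| 10% | 0.44 | 1.80 | 27.5% | 0.49 |

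**5. Regional differences constant over time.** With 25% or 50% of the between-unit variance held as a fixed regional difference, the SE ratio is 1.01 or 1.02, type I error is 5.2% or 5.4%, and power stays at 0.92. The comparison is largely within unit, so a constant regional level nearly cancels.

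**The case against.** The strongest reply is that the inflation is conditional and its size unknown. The article reports no between-period correlation. If rates move only with the common trend and case mix, the 5% level holds. This stands, and it limits the point to saying that the error rate is unprotected.

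A second reply concerns the evidence for regional drift. Shared training days and regional feedback are parts of the intervention, and a shared start date is the exposure itself. Under a null of no effect they cannot create drift, so they are weak support for a false-positive argument. The regions are also broad groupings, with units spread over clinical senates, sizes and types. This stands too.

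Third, drift of the assumed size does not swamp the sampling error in the unit-level cases. Ratios of 1.13 and 1.25 mean that drift supplies 1 − 1/1.13² = 22% and 1 − 1/1.25² = 36% of the true variance. That is material but not dominant.

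Fourth, small-sample reference distributions and secondary models commonly belong to an analysis plan, which is not shown, so their absence is no finding. A permutation test over the 4! = 24 region orders has a smallest p-value of 1/24 = 0.042 and would make a poor decision rule. Neither is needed here. The point survives because the article does commit itself to a specific random-effects structure and to a power figure that depends on it.

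**Conclusion.** The point holds in conditional form. Allocation is by region, power and model are by unit, and the planned model leaves no room for unit or regional rates that vary over time in their own way. If such variation exists, the planned standard error is too small.

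For unit-by-period shares of 5 to 20%, type I error is about 8 to 18% and power 0.86 to 0.66. For region-by-period shares of 1 to 10%, type I error is about 8 to 28%. These figures rest on assumed shares, ICC 0.0062, a two-sided 5% level and a linear approximation to the logistic model. The quoted ICC interval alone moves the 10% unit-by-period case from 6.7% to 25.6%. The direction is firm; the size is not.

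A reader might infer two stronger things. One is that the 5% level is broken simply because four regions were randomised. The documents do not show this, since constant regional differences leave it nearly intact. The other is that drift takes power from 0.92 to about 0.62, 0.54 or 0.43 at autocorrelations of 0.95, 0.90 and 0.80. Those values arise only when the roll-out quarters in Table 1 are left out, where power is already 0.73 without drift. Against the 0.92 baseline, the fall due to drift alone is to 0.86, 0.78 and 0.66.

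This is a cheap improvement, not a fatal flaw.

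**What to change.** In the model paragraph of Data analysis, add a unit-by-period random effect to the unit random intercept in the primary model. Report a sensitivity analysis with a region-by-period random effect, and note that its variance rests on only four regions. The unit-by-period term does not by itself cover drift shared across a region, so both are needed.

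In the power paragraph, report power for cluster autocorrelations of 0.80 to 0.95 beside the 0.92 baseline (about 0.66 to 0.86 on the inputs above), and stop presenting the lower ICC limit as a stress test.

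The cost is a change of wording and a re-run of the power table, with no new data and no change to conduct. The downside is wider confidence intervals and a lower stated power.
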